#### Study Procedures

##### Randomization

Following informed consent and the baseline assessment (discussed later), we will use a web-based system to randomize women (1:1) to the *i.ARTs* intervention arm (n=90) or to the standard-of-care control arm (n=90). Neither participants nor researchers will be blind to study condition. Women in the control arm will receive standard of care as it exists at the time of LAI ART roll out: providers will offer women information about LAI ART and may strongly suggest which option she should choose. Women who participated in the focus groups will not be eligible for inclusion.

Women in the intervention arm will use *i.ARTs* as part of their regular participant visit. While the complete content of *i.ARTs* will be finalized in phase 2, the web-based *i.ARTs* app will guide WWH through the following activities: (1) provide education on different ART modalities, (2) utilize value clarification methods to guide women in ranking the prominence of relevant barriers and facilitators that may impact adherence to various ART modalities, (3) collect information on participant health history, (4) generate a suggested ART modality based on previous steps, (5) assist WWH in developing questions for their health care providers, and (6) generate an individual profile description as well as individualized suggestions to support adherence based on the modality selected (eg, a woman may be profiled as having transportation challenges; *i.ARTs* would suggest solutions—arranged transportation or transportation vouchers—that the clinic could employ to address these challenges). Participants will take a printout of this profile to their clinic visit with their provider. Intervention arm participants will receive US $15 for *i.ARTs* use.

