##### Assessments

All women enrolled in the study will complete a baseline survey following informed consent and a follow-up survey immediately after their clinical visit. Surveys will be administered on tablets in a private room within the clinic and will use REDCap for data collection. Each survey will take approximately 25 minutes to complete, and women will receive US $25. Survey measures are described later and in Table 2.

A subsample of 20 intervention (*i.ARTs*) arm women and 10 providers will be randomly chosen to participate in an exit interview. This interview will occur either at the baseline visit or up to 1 month after *i.ARTs* use at the participant’s convenience. We will select every fourth woman in the intervention arm to complete the exit interview. Providers will be selected based on the number of *i.ARTs* participants they served in the first year of the pilot (we will randomly select 10 providers from all providers who serve above the median number of *i.ARTs* clients, which ensures that providers will have sufficient experience with the tool to provide feedback) and exit interviews with providers will be conducted in the final 3 months of data collection. These interviews will focus on patient and provider experiences with *i.ARTs* acceptability, feasibility, and usability, and the most useful ways to improve its integration into clinical practice. This will also include discussions of how women shared the results from the patient decision aid with their provider. Exit interviews will take approximately 30 minutes and participants will be provided US $30 in compensation.

The study will also use all 180 participants’ electronic medical records (EMRs) to assess the impact of the intervention on clinical outcomes (Table 2). The informed consent process will include the EMR abstraction release form and detailed information about the data abstraction process. Study staff will abstract data on viral suppression (all women), ART modality, clinic attendance (all women), and medication refill data (women on oral ART) from EMRs into a REDCap database. Abstraction will include data from 1-year prebaseline to 6 months postbaseline. This timeline is based on the frequency of HIV clinic visits (ie, approximately every 3 months) to ensure that women have at least one visit in the follow-up period.

**Table 2 table2:** *i.ARTs*^a^ pilot study measures in phase 3.

Outcomes			Description of measures

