**Primary**			Assessed after *i.ARTs* use among women using i.ARTs (n=90)
	Feasibility	Adaptation of Thabane et al’s [59] framework [60,61] for assessing pilot studies: Process, Resources, Management, Science	
	Acceptability and usability	Acceptability [62] and CSQ-8^b^ [63] to measure satisfaction with *i.ARTs*; exit interviews about *i.ARTs* features/protocol [62]	
**Secondary**			Assessed in baseline survey and postvisit survey for all women (n=180)
	Decisional conflict	Decisional Conflict Scale (16 items) [52]; satisfaction with the chosen method [64]	
**Tertiary**			Assessed 1-year prebaseline, at baseline, 3 months, and 6 months (all women; n=180)
	Viral suppression	Viral suppression, defined as viral load below limit of detection per assay used	
	Medication refills	Missed doses; report of medication refills/pharmacy pick up (WWH^c^ on oral ART^d^)	
	Clinic attendance	Missed or cancelled medical visits (<2 visits in a 6-month period for oral ART; missed monthly visit for LAI^e^ ART)	
	ART modality	Adoption of LAI among patients who are virally suppressed	
**Moderators**			Assessed at baseline
	Sociodemographics	Race/ethnicity, age, housing stability, education, employment, income, distance from clinic, relationship status, children	
	Depression/anxiety	PHQ-8^f^ (depression) [65]; GAD-7^g^ [66]	
	Substance use	ASSIST^h^ [67], an 8-item measure of problematic substance use	
	Stigma/discrimination	MDS^i^ to measure racial discrimination [68]; HIV-related stigma	
	Self-efficacy	HIV-ASES^j^ [38]	
	ART-related knowledge	Adaptation of Feldman’s [69] scale of oral ART knowledge; BMQ^k^ [70]	

^a^*i.ARTs*: i.ART+support.

^b^CSQ-8: 8-item Client Satisfaction Questionnaire.

^c^WWH: women with HIV.

^d^ART: antiretroviral therapy.

^e^LAI: long-acting injectable.

^f^PHQ-8: 8-item Patient Health Questionnaire.

^g^GAD-7: 7-item General Anxiety Disorder scale.

^h^ASSIST: Alcohol, Smoking and Substance Involvement Screening Test.

^i^MDS: 10-item Multiple Discrimination Scale.

^j^HIV-ASES: HIV Treatment Adherence Self-Efficacy Scale.

^k^BMQ-18: 18-item Beliefs and Medicines Questionnaire.

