#### Study Outcomes and Measures

All study outcomes are summarized in Table 2. *Primary outcomes* include *i.ARTs feasibility, acceptability,* and *usability.* To assess feasibility, we will adapt Thabane et al’s [59] framework [60,61]. For *acceptability and usability,* we will use the 8-item Client Satisfaction Questionnaire (CSQ-8) to assess participants’ attitudes, burden, ethics, coherence, opportunity cost, perceived effectiveness, and self-efficacy [63]. The *secondary outcome* is ART-related decisional conflict, a 16-item scale scored from 0 to 100 [52]. Scores of 0-25 are associated with “implementing decisions” and scores of 37.5-100 are associated with “decision delay/feeling unsure.” *Tertiary outcomes* are exploratory, and consist of information extracted from EMRs, including viral suppression at the most recent visit in the prior 6 months, ART modality, medication refills (oral ART), and clinic attendance in the prior 6 months.

In addition to the outcomes, the baseline survey will measure moderators associated with adherence, including sociodemographics, depression, anxiety, substance use, HIV-related stigma and discrimination, self-efficacy, and ART-related knowledge.

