#### Analysis

The primary outcomes of feasibility, acceptability, and usability will be assessed descriptively. We will compare ART-related decisional conflict, clinic attendance, viral suppression, and medication refills between and within the 90 women in each arm (baseline vs postvisit surveys and EMR data at 3 and 6 months). For normally distributed data, we will first use *t* tests to compare the 2 arms and then use regression methods to develop a multivariable model of the outcome, with arm membership as the principal covariate, while controlling for the moderators listed in the previous sections and in Table 2. For nonnormally distributed data, we will employ chi-square tests and logistic regression; distributional properties of the outcome will determine the type of logistic regression (eg, binary, multinomial, or ordinal logistic regression models). We note that these are examples and the final approach will be determined based on the distribution of the data.

The primary analysis will use an intent-to-treat approach with the use of *i.ARTs* as a 1-time exposure, with α=.05, and 2-sided tests. The number of moderators included in the regression model will be used to make a Bonferroni adjustment to the α value. A secondary efficacy analysis will explore actual treatment taken. Our exploratory tertiary outcomes of viral suppression, clinic attendance, chosen ART modality, and medication refills will compare both between and within *i.ARTs* and control arm women (ie, baseline and postvisit surveys and EMR data at 3 and 6 months); we will also examine these outcomes for women who do not change regimens. We will use prebaseline EMR data to control for previous viral load. We will also compare how many women in each arm change modalities postbaseline to assess *i.ARTs’* accuracy in identifying which HIV treatment modality is the best match. Sensitivity analyses will determine whether assumptions associated with each model are defensible.

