### Expected Challenges

As this study is set in real-world clinical settings, we expect challenges to incorporating *i.ARTs* delivery into existing clinical workflows. These include considerations such as available space for participants to complete *i.ARTs*, tech support for the computerized tool and printout, staffing resources, and limited clinician time with each patient to discuss the decision aid results. The study team will work with the clinic staff to determine how to ensure efficient delivery of *i.ARTs* in the clinical setting. Exit interviews will be used to collect data on these challenges to inform further scale-up or dissemination efforts of *i.ARTs* outside of the Miami-based clinic*.*

As LAI ART is being administered in a real-world setting, participating clinicians are subject to existing, and possibly changing, FDA approvals. While phase 3 trials are currently testing LAI ART for nonadherent patients, *the FDA-approved LAI ART formulation is only for virally suppressed patients*. To ensure *i.ARTs* incorporates all relevant drivers of ART use for all women, we aim to include nonadherent women in aim 3, pending FDA approval. If FDA approval only exists for virally suppressed WWH when aim 3 starts, then we will limit the pilot test to that population. Should FDA approval for nonadherent patients begin in the middle of the pilot, we may adjust eligibility criteria to ensure a standard participant population throughout the pilot period. The study team will carefully monitor developments in ART treatment technologies and adapt accordingly. In addition, LAI ART was initially approved as a monthly injection, and the US FDA has approved a bimonthly (ie, every 8 weeks) formulation of LAI ART. This may also affect women’s preferences as the study is rolled out.

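### Refills are recorded only for women on oral ART, a group partly formed after randomisation, yet they are compared between arms as if all 90 women in each contributed

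*Protocol article*

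**What the plan says.** All places are in the protocol article, Phase 3.

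- **Collection.** Assessments marks viral suppression and clinic attendance as abstracted for all women, but restricts "medication refill data (women on oral ART"). The refill row of Table 2 (missed doses, "report of medication refills/pharmacy pick up") carries the same restriction. Study Outcomes and Measures repeats it: "ART modality, medication refills (oral ART), and clinic attendance in the prior 6 months".
- **Stated population.** The heading of the tertiary block in Table 2 reads "Assessed 1-year prebaseline, at baseline, 3 months, and 6 months (all women; n=180").
- **Comparison.** The Analysis section says: "We will compare ART-related decisional conflict, clinic attendance, viral suppression, and medication refills between and within the 90 women in each arm", with EMR data at 3 and 6 months.
- **Timing of the choice.** Under Randomization, women are allocated first. Those in the intervention arm then use i.ARTs, which has them rank barriers to adherence and will "generate a suggested ART modality based on previous steps". ART modality is itself a follow-up outcome in Table 2.

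**The concern.** A woman who moves to LAI ART has no refill value at 3 or 6 months. The refill denominator at those times is the set of women who stayed on, or returned to, oral ART, and one arm has used a tool meant to inform exactly that decision. If i.ARTs alters which women leave oral ART, and leaving is related to how well they take pills, the two remaining groups differ in make-up even if no woman's adherence changed. An observed gap could then be read as an effect of i.ARTs on adherence. The abstract and Study Design both name refills among the outcomes to be associated with receiving i.ARTs, so such a signal could carry into the case for a later trial.

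**Working it through.** **The protocol's own figure.** The only design calculation is for decisional conflict: means 21 (SD 16) and 28 (SD 18), 90 per arm, 80% power. The pooled SD is √((16² + 18²)/2) = 17.03, which gives 78.7% power, close to the stated value. It does not bear on refills, for which the protocol gives no figure.

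**Inputs for refills**
- 90 women per arm (Study Design).
- Share with poor adherence, p. Power Analysis and Sample Size cites 35% of US women as not adherent after 6 months. That is a national figure and not a refill rate, so p = 10% is also shown as an assumption.
- LAI uptake among poor adherers (u_N) and among the rest (u_A). The protocol gives neither, so all uptake values are assumptions.
- No effect of i.ARTs on any woman's adherence.

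**Formula.** Non-adherence among women still on oral ART = p(1 − u_N) / [p(1 − u_N) + (1 − p)(1 − u_A)]. The number on oral ART is 90 times the denominator.

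**Results**
1. p = 35%, u_A = 20% in both arms, u_N = 50% (i.ARTs) and 20% (control).
   - i.ARTs: 0.35 × 0.5 = 0.175; 0.65 × 0.8 = 0.52; 0.175/0.695 = 25.2%, n ≈ 63.
   - Control: 0.35 × 0.8 = 0.28; 0.28/0.80 = 35.0%, n = 72.
   - Apparent benefit of 9.8 points. Its standard error is √(0.252 × 0.748/63 + 0.35 × 0.65/72) ≈ 0.079, so the gap is about 1.2 standard errors.
2. Same uptake, p = 10%.
   - i.ARTs: 0.05/(0.05 + 0.72) = 6.5%. Control: 0.08/(0.08 + 0.72) = 10.0%.
   - Apparent benefit of 3.5 points.
3. u_N = u_A within each arm, for example 40% against 20%. The uptake factor cancels, each arm returns p, and the gap is zero.
4. p = 35%, all women eligible to switch, better adherers switching more under i.ARTs: u_A = 50%, u_N = 20%, against 10% for everyone in control.
   - i.ARTs: 0.28/(0.28 + 0.325) = 46.3%. Control: 35.0%.
   - Apparent harm of 11.3 points, so the arithmetic fixes no direction.
5. Equal overall uptake of 30% in both arms, opposite selection: control u_A = 38.6%, u_N = 14.1%; i.ARTs u_A = 20%, u_N = 48.6%.
   - Adherence among oral women is 57.0% in control and 74.3% with i.ARTs.
   - Similar numbers left on oral ART do not show that the groups are comparable.

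**Error rate of a test.** Simulation with 40,000 replicates, p = 35%, two-sided 5% test. With 10% uptake throughout control, and 20% (adherent) and 50% (non-adherent) under i.ARTs, the oral-only test rejected in 24% of replicates. A test on the underlying adherence of all 90 per arm rejected in about 5%. With uptake of 20% against 40% unrelated to adherence, the oral-only test also rejected in about 5%.

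**The case against.** Several points on the other side have force.

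- **Refills are exploratory.** They are tertiary, do not drive the sample size, and sit in a pilot that speaks of associations. This stands and limits the weight of the point. It does not make the comparison interpretable.
- **Intent-to-treat.** A reader might infer that the protocol breaks its own intent-to-treat commitment. The Analysis section attaches that approach to the primary analysis and describes the exploratory tertiary outcomes separately, so the contradiction is one of denominators only. Even there, the Table 2 row does qualify its block heading; the plainer conflict is with the Analysis wording.
- **Regulatory limit on switching.** Expected Challenges notes that "the FDA-approved LAI ART formulation is only for virally suppressed patients". A reader might infer that only good adherers could switch, so that i.ARTs would look harmful on refills. The same section says that if approval is still so limited when this phase starts, the pilot will be restricted to suppressed women. A mixed sample with an ineligible share is then not the planned one. The document does not support that reading or any predicted direction of bias.
- **The 35% may be too high.** In a sample limited to suppressed women, poor refill adherence could be much lower and the gap smaller, as the 10% case shows.
- **Adjustment.** Regression on baseline moderators, including adherence self-efficacy, and control for previous viral load give partial protection, and the illustrations are for a crude comparison. Adjustment does not restore the randomised comparison. The extra look at women who do not change regimens conditions on the same kind of post-randomisation event.
- **A separate analysis plan may handle switches.** It may, but the article itself fixes both the restricted collection and the full-arm comparison.

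**Conclusion.** The point holds in conditional form. Refills are collected for a subgroup that, after baseline, depends on a choice i.ARTs is meant to inform, and the Analysis section compares them as though the full randomised arms contributed. A between-arm difference can therefore arise with no effect on adherence, provided the link between switching and adherence differs by arm. Because i.ARTs works through adherence barriers before suggesting a modality, such a difference is plausible, but nothing in the document shows that it will occur. The illustrated size runs from zero, through about 3.5 points (10% poor adherence), to about 10 points (35%), all on assumed uptake rates. The primary outcomes, decisional conflict and the sample size are untouched. The correction is worth making before the trial starts, and it is not a flaw in the trial's main purpose.

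**What to change.** **Main change**
- In Table 2 and the Analysis section, state the refill denominator as women on oral ART at the time point concerned.
- Report refills descriptively, with the number on oral ART by arm at each time point, and with no between-arm test or claim of effect. Bring the abstract and Study Design into line.
- Base between-arm conclusions on adherence on outcomes recorded for all 180 women and analysed by randomised arm: viral suppression and clinic attendance. Table 2 scores missed attendance by a different rule for each modality, so viral suppression is the cleaner of the two.

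This costs wording only, plus the loss of a refill test that could not be interpreted.

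**Optional addition**
- An exploratory measure of days covered by any ART, from refills and injections, for every randomised woman. Assessments does not list injection dates among the abstracted items, so they would have to be added and a coverage rule set in advance. Dispensed pills and administered injections are not equivalent measures, so switching could move the score through measurement alone; this caveat should accompany the result.

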**Figure 1 figure1:**
[figure not shown]
Study overview. *i.ARTs*: i.ART+support; LAI ART: long-acting injectable ART; MWCCS: MACS/WIHS Combined Cohort Study; WWH: women with HIV.

**Table 1 table1:** Overview of data sources and participants.

Phase	Data source	Participants	Scope of data	Purpose
1	MWCCS^a^ 2020 cohort survey	1500 WWH^b^ at 9 MWCCS sites	WWH perspectives on LAI ART^c^ and decision making; identify relevant barriers and facilitators to LAI ART uptake; characteristics of women who are most likely to adhere to LAI ART	Generate *i.ARTs*^d^ content
1	Provider interviews	45 medical/social service providers at MWCCS sites	Provider perspective on characteristics of women most likely to adhere to LAI ART; reasons providers would not offer LAI ART to a woman for whom it is clinically indicated; provider perceptions of multilevel barriers and facilitators to WWH’s ART use	Generate *i.ARTs* content
2	Focus groups	MWCCS providers, WWH in Miami, Florida	Feedback on successive iterations of *i.ARTs*	Develop and refine *i.ARTs* content
3	Baseline and postvisit survey	180 WWH (90 from the intervention/*i.ARTs* arm and 90 from the control arm)	Information on decisional conflict (baseline and post), acceptability and satisfaction (post only), and sociodemographic and behavioral moderators (baseline only)	Assess *i.ARTs* acceptability and usability outcomes, assess impact of moderators
3	Exit interviews	20 WWH who receive *i.ARTs* and 10 providers	WWH and provider perspectives on *i.ARTs* tool	Assess *i.ARTs* feasibility, usability, acceptability
3	Electronic medical record data	180 WWH	*i.ARTs* adherence data for study participants, including clinic visits, medication refills, and viral load data	Preliminary impact of *i.ARTs* data on treatment-related outcomes

^a^MWCCS: MACS/WIHS Combined Cohort Study.

^b^WWH: women with HIV.

^c^LAI ART: long-acting injectable antiretroviral therapy.

^d^*i.ARTs*: i.ART+support

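### The protocol names chosen ART modality as an outcome but defines it as LAI adoption in the medical record, and Table 2 times satisfaction with the chosen method before any choice is made

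*Protocol article*

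**What the plan says.** **Modality.** Study Design (Phase 3) includes the chosen ART modality among the outcomes to be related to receipt of the aid. The Analysis section repeats it: "Our exploratory tertiary outcomes of viral suppression, clinic attendance, chosen ART modality, and medication refills will compare both between and within" the two arms. The parenthesis that closes that clause gives the baseline and postvisit surveys, together with EMR data at 3 and 6 months, as the sources for the whole group of tertiary outcomes.

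Study Outcomes and Measures says instead that the tertiary outcomes consist of information extracted from EMRs, with ART modality among them. The Assessments section agrees: "Study staff will abstract data on viral suppression (all women), ART modality, clinic attendance (all women), and medication refill data". Table 2 defines the modality outcome as adoption of LAI among virally suppressed patients, read 1 year before baseline, at baseline, and at 3 and 6 months.

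Under Randomization, the app in the intervention arm builds its individual profile on the modality selected. No counterpart is described for controls.

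**Satisfaction.** The secondary block of Table 2 holds "Decisional Conflict Scale (16 items) [52]; satisfaction with the chosen method [64" under the heading "Assessed in baseline survey and postvisit survey for all women (n=180". Table 1 gives the scope of the same two surveys as "Information on decisional conflict (baseline and post), acceptability and satisfaction (post only".

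**Order of events.** "Following informed consent and the baseline assessment (discussed later), we will use a web-based system to randomize women (1:1", and "All women enrolled in the study will complete a baseline survey following informed consent and a follow-up survey immediately after their clinical visit".

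**The concern.** The aid exists to help women choose between oral and LAI treatment, so the choice made at the visit is the outcome closest to what the aid does. Choosing LAI and being on LAI some months later are different events. The protocol's Introduction names what can come between them: the viral suppression requirement, transportation, unstable work schedules and provider willingness. If the only usable record is adoption, a woman who chose LAI and never started it falls in the same category as one who chose oral. A between-arm difference in adoption then mixes an effect on choice with an effect on access.

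This also touches a second planned use. The Analysis section compares how many women change modality after baseline, in order to judge how accurately the aid identifies the best match. Without a record of the initial choice, failure to start LAI cannot be separated from a decision to stay on oral treatment.

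The satisfaction item has a timing problem. A baseline rating of the chosen method has no choice to refer to; at most it describes the current regimen. If it were compared with the postvisit rating, the two scores would describe different things.

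**Working it through.** **1. Modality, section by section.**

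| Place | Term used | Source given |
|---|---|---|
| Study Design (Phase 3) | chosen modality | none stated |
| Assessments | ART modality | EMR |
| Table 2, tertiary | adoption of LAI, suppressed women | schedule only: prebaseline, baseline, 3 and 6 months |
| Study Outcomes and Measures | ART modality | EMR |
| Analysis | chosen modality | baseline and postvisit surveys, plus EMR at 3 and 6 months, for all tertiary outcomes together |

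The Analysis parenthesis cannot apply item by item. It also covers viral suppression and refills, which Assessments assigns to the EMR. It therefore does not establish a survey source for choice, although it does leave one possible. Neither the Table 1 scope of the surveys nor Table 2 lists a measure of the modality decided on at the visit.

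**2. Satisfaction, both readings of Table 1.**

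- If satisfaction in Table 1 includes satisfaction with the chosen method, Table 1 (post only) contradicts Table 2 (baseline and post).
- If it means only the CSQ-8 satisfaction with the aid, there is no contradiction. Table 2 then still times satisfaction with the chosen method before randomization and the visit, and Table 1 leaves that measure out.

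On either reading Table 2 needs correcting.

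**3. The plan's own power figure.** The protocol states 80% power at 90 per arm for decisional conflict: 21 (SD 16) against 28 (SD 18), two-sided α=.05.

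- SD = √((16² + 18²)/2) = √290 = 17.03
- z = 7 / (17.03 × √(2/90)) = 2.757
- Power = Φ(2.757 − 1.960) = 78.7% (78.3% with the noncentral t)

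This agrees with the stated 80% to within 2 percentage points. The present point does not alter it. The protocol gives no power figure for modality.

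**4. Illustration of choice against adoption.** All proportions are assumptions. Suppose 45% (i.ARTs) and 30% (control) choose LAI, a share s of choosers has started by the EMR reading, and s is the same in both arms. With 90 per arm and two-sided α=.05:

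- h = 2·arcsin√p₁ − 2·arcsin√p₂
- Power ≈ Φ(h·√(90/2) − 1.960)

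| s | i.ARTs | Control | Difference | h | Power |
|---|---|---|---|---|---|
| 100% (choice itself) | 45% | 30% | 15 points | 0.311 | 55% |
| 80% | 36% | 24% | 12 points | 0.263 | 42% |
| 60% | 27% | 18% | 9 points | 0.217 | 31% |

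**5. Unequal start rates.** If the aid also eases access, s differs by arm. With 80% starting in the i.ARTs arm and 60% in control, adoption is 0.45 × 0.80 = 36% against 0.30 × 0.60 = 18%. That is an 18-point difference, larger than the 15 points in choice. Adoption can therefore understate or overstate the effect on choice, and without the choice recorded the data cannot show which.

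**The case against.** **The postvisit survey is a named source.** A reader might infer that choice can come only from the EMR. The documents do not support that. The Analysis section attaches the postvisit survey, which women in both arms complete, to a group of outcomes that includes chosen modality. What stands is narrower: the sections disagree, and no listed measure fills the gap.

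**Item lists are commonly left out of an article.** A missing questionnaire item does not prove that choice goes unrecorded, and a survey asking about satisfaction with the chosen method may well identify that method. This is fair. But Assessments refers the reader to Table 2 for the survey measures, and Table 2 does define the modality outcome, as adoption. That conflict of definition is in the printed text.

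**Adoption is a legitimate outcome, and access is part of the mechanism.** Under Randomization, the app proposes ways around barriers such as transportation, so the step from choosing to starting is partly something the aid is meant to change. This stands. It defeats the simple claim that access barriers only dilute the effect, and it is a reason to keep adoption. It is also a reason to record choice separately.

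**Suppression is already handled.** Table 2 restricts the outcome to suppressed women, and Expected Challenges would limit the pilot to them if approval stays so limited. This removes one of the filters between choosing and starting, not the others.

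**No change score for satisfaction is announced.** A reader might infer from Table 2 that a baseline-to-postvisit comparison of satisfaction is planned. The Analysis section does not name satisfaction, and Study Outcomes and Measures gives decisional conflict alone as the secondary outcome. The finding is the baseline timing, not a faulty planned comparison.

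**Conclusion.** The point holds as a conflict of definition and timing. The protocol calls an outcome chosen modality and defines it as EMR-recorded adoption of LAI. No listed survey measure records the choice, and the only same-day selection described belongs to the intervention arm. Table 2 times satisfaction with the chosen method at a baseline that precedes any choice under study.

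The documents do not show that choice will certainly go unrecorded, nor that a satisfaction change score will be analysed.

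The size is modest. The tertiary outcomes are exploratory, the primary outcomes are descriptive, and neither the sample size nor the stated power changes. The 9- and 12-point figures and their power values rest on assumed choice and start rates, equal start rates in the two arms, and all 90 women per arm counting. They show the mechanism and do not estimate anything about this trial. The change is worth making because it is cheap and because a choice not recorded on the day cannot be reliably recovered later.

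**What to change.** 1. Add one item to the postvisit survey in both arms: the modality decided on at today's visit (oral, LAI, undecided). Use it as the chosen modality outcome. If the full survey already contains such an item, list it in Table 2.
2. Keep EMR adoption at 3 and 6 months as a separate received modality outcome.
3. Reconcile Table 2, Study Outcomes and Measures, and Analysis so that each of the two outcomes has one name, one source and one schedule.
4. In Table 2, make satisfaction with the chosen method postvisit only, and state in Table 1 whether its satisfaction entry covers this measure, the CSQ-8, or both.

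The cost is one tablet item in a survey planned for all 180 women, plus corrections to the text and tables. The downside is one more self-reported variable, which may differ from the chart.
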